#### TDMS data

We will calculate levels of arousal and pleasure from TDMS scores. At first, we will confirm that the sample represents the normal population, i.e. shows a normal distribution (all *p* values for arousal and pleasure level in both intervention conditions have to be > 0.05 at Shapiro-Wilk test). In addition, we will check if the levels of arousal and pleasure are not different between sessions (comparing results before 1PP and before 3PP) so that all participants start from the same baseline level. That means we can proceed to subtract the results after the intervention from the results before the intervention (after-before).

By performing an ANOVA comparing 1PP and 3PP, we predict finding an increased level of arousal (but not necessarily of pleasure) after the vHIE, especially after the intervention in 1PP, as described in previous studies [17].

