#### Two-Dimensional Mood Scale

The Two-Dimensional Mood Scale (TDMS) is an effective measure to record changes in psychological mood states. The TDMS was developed as a psychometric scale using eight mood-expressing items (energetic, lively, lethargic, listless, relaxed, calm, irritated, and nervous) that, when combined, express mood states of pleasure and arousal [54]. We will ask participants to rate their present psychological state using a six-point Likert scale from 0 = “Not at all” to 5 = “Extremely” [17]. They will repeat the TDMS right before the pre-Stroop task (before the vHIE), as well as right after the post-Stroop task (after the vHIE) for each session (1PP and 3PP) (see Fig. 2a).

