### Sample size

Considering that the main outcome of this study is the RT of the Stroop task (which is claimed by many to be one of the indicators of executive performance), which typically has a moderate effect, we calculated a sample size of 28 individuals (with α error probability set at 0.05 and power set at 0.8). We decided to recruit 30 participants to eventually control for drop-off.

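### The TDMS change-score analysis is made to follow from non-significant normality and baseline pre-tests, which cannot confirm either condition and would often fail by chance

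*Protocol article*

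**What the plan says.** All of this is in the protocol article, under Statistical analysis, TDMS data, unless another section is named.

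- **Normality.** The stated aim is "At first, we will confirm that the sample represents the normal population, i.e. shows a normal distribution". The criterion is strict: all p "values for arousal and pleasure level in both intervention conditions have to be > 0.05 at Shapiro-Wilk test".
- **Baseline.** Next, "we will check if the levels of arousal and pleasure are not different between sessions (comparing results before 1PP and before 3PP"), and the purpose given is "so that all participants start from the same baseline level". No test or threshold is named for this step.
- **Consequence.** The next sentence begins "That means we can proceed to subtract the results after the intervention from the results before the intervention (after-before"). The change scores are then compared between 1PP and 3PP by ANOVA.
- **Occasions.** The section on the Two-Dimensional Mood Scale has the scale completed twice per session: "They will repeat the TDMS right before the pre-Stroop task (before the vHIE), as well as right after the post-Stroop task (after the vHIE").
- **Status.** The Outcomes section lists TDMS among the additional outcomes, neither primary nor secondary. The Correlations section uses TDMS results once more, in relation to the Stroop data.

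**The concern.** Three things are wrong with using these tests as the footing for the analysis.

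1. A non-significant result is read as proof. Failing to reject normality, or failing to find a mean difference between sessions, shows neither. A comparison of group means also cannot show that every participant starts at the same level.
2. The wording points to the arousal and pleasure levels, tested before change scores exist. A paired comparison of change rests on the distribution of each person's difference in change between 1PP and 3PP. The levels can look non-normal while that difference is well behaved, and the reverse.
3. The order of conditions is randomised, so a before-score difference between conditions is expected to be chance. The useful response is to adjust for it, not to make the analysis depend on its absence.

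At stake is a pre-specified TDMS comparison whose stated footing would fail quite often when nothing is amiss, and which would claim a confirmation the tests cannot give when it passes.

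**Working it through.** The protocol gives no failure rate for these checks, so there is no figure of its own to reproduce.

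**Inputs**
- Normality threshold: p > 0.05 for every test (TDMS data).
- Number of normality tests: 2 scales × 2 conditions = 4 for one set of scores. If before and after scores are both tested, 2 × 2 × 2 = 8. The section does not say which time points are meant.
- Baseline tests: 2 (arousal, pleasure). The 0.05 two-sided threshold is an assumption.
- Sample: 30 recruited (Sample size: "We decided to recruit 30 participants to eventually control for drop-off").

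**Chance of at least one significant pre-test when normality and equal baselines both hold**

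For k independent tests at 0.05 this is 1 − 0.95^k.

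| Tests | k | Chance of failure |
|---|---|---|
| Baseline only | 2 | 1 − 0.95² = 9.8% |
| Normality, one set of scores | 4 | 1 − 0.95⁴ = 18.5% |
| Normality, before and after | 8 | 1 − 0.95⁸ = 33.7% |
| 4 normality + 2 baseline | 6 | 1 − 0.95⁶ = 26.5% |
| 8 normality + 2 baseline | 10 | 1 − 0.95¹⁰ = 40.1% |

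**Does independence drive this?** Little. The check was a simulation with n = 30, truly normal scores, equal baselines, within-scale correlation 0 to 0.8 and arousal–pleasure correlation 0 to 0.6, with 3,000 runs per setting. It gives about 24–28% for 6 tests and 35–40% for 10.

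**Does passing confirm anything?** At n = 30:
- Shapiro-Wilk rejects only about 24% of samples from a t distribution with 5 df, 25% from a gamma with shape 8, 39% from a uniform and 44% from a gamma with shape 4. Most non-normal samples of these kinds pass.
- A paired t-test has power of about 19%, 36% and 56% for true standardised baseline differences of 0.2, 0.3 and 0.4. It therefore misses 81%, 64% and 44% of them.

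**What does a chance baseline difference do?** For one person and one scale, let Y be the 1PP minus 3PP difference in after scores and X the same difference in before scores. The change-score comparison uses Y − X. With order randomised (15 participants per order) and no carry-over, X has expectation zero, so Y − X is not biased by it on average. If X and Y have equal variance s² and correlation r, then Var(Y − X) = 2s²(1 − r). After adjustment the variance is s²(1 − r²). The ratio of adjusted to unadjusted variance is (1 + r)/2, which is below 1 whenever r is below 1. The cost of not adjusting is precision.

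**The case against.** **The percentages are not the protocol's.** True. It prints a threshold for normality only; the test counts and the baseline threshold are assumptions. The part that rests on a printed threshold is the 18.5% or 33.7%, and even there the choice between 4 and 8 tests is a reading. A reader might take 26–40% as a property of the plan; it is a conditional range. Exact normality is also hypothetical for a scale built from eight items rated 0 to 5. That objection does not help the rule: rounding normal scores to integers raises the Shapiro-Wilk rejection rate to about 10% per test at an assumed SD of 3, and 6% at an SD of 5.

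**Nothing says the analysis is abandoned if a check fails.** Also true. A reader might infer that the rule blocks the TDMS analysis. The text does not go that far: it describes the expected path, the baseline step is worded more softly than the normality step, and a fallback could sit in an analysis plan that is not shown. What stands is that the protocol presents non-significance as confirmation and as the reason it may proceed.

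**Baseline differences might be said to bias the result.** A reader might infer that real differences too small to be significant leak into the change score. Under randomised order this is not supported, as the working shows. Carry-over into the second session's before score is the exception, and a reason to keep looking at before scores descriptively.

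**Which scores are tested for normality is not spelled out.** Correct. The reference to levels, and the placing of the test before subtraction, suggest raw scores but do not settle it.

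**An ANOVA on change scores is valid in a randomised cross-over.** It is. The adjusted model is a gain in efficiency; the error lies in the preconditions.

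**Conclusion.** The point holds in a limited form. The protocol makes the TDMS change-score comparison follow from non-significant pre-tests that confirm neither normality nor equal baselines at about 30 people, and that appear to examine the wrong quantity. With nothing wrong, the normality rule alone fails in about 19% (4 tests) or 34% (8 tests) of trials. With two baseline tests at an assumed 0.05, the figures are about 26% or 40%. All four assume independence; realistic correlation lowers them only slightly.

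The reach is small. TDMS is an additional outcome, and its one further use is the relation with Stroop data in the Correlations section. The point should not be extended to the Stroop baseline comparison: the section on RT and ER calls that check supplementary, and the primary analysis does not depend on it. This is a free improvement, not a threat to the trial's main conclusion.

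**What to change.** In the TDMS data section:

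- Remove the Shapiro-Wilk and baseline-equality tests as conditions for the analysis, together with the statements that they confirm normality or a common starting level. Report before scores by condition and session descriptively.
- For arousal and pleasure separately, compare after scores in 1PP and 3PP within person, adjusting for that session's before score and for session order.
- Check the residuals of that model, and give a Wilcoxon signed-rank test on the paired difference in change as a sensitivity analysis.

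The pre-tests then have no chance failure rate, because nothing depends on them. The cost is a few sentences and a slightly richer model. Before and after scores are already collected in both sessions, so no new data or participants are needed.

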#### Correlations

The crucial correlation for our hypothesis concerns the relationship between Stroop task and fNIRS data: we will first investigate the cortical regions mainly activated during the Stroop task before the vHIE in both intervention conditions, as a baseline reference. Then, the (incongruent – neutral) contrasts for the two intervention conditions will be averaged as substrates for ROI analysis. The (incongruent – neutral) contrast for RT and ER with O2Hb changes in all ROIs will be treated with a repeated-measures ANOVA considering as factors intervention condition (1PP and 3PP) and time (before and after the vHIE).

In addition to that, as described in previous studies, we will examine the relation between Stroop data and cortical activation or TDMS results in a binominal manner [22, 49]: for each variable the following contrast will be calculated {[(incongruent – neutral) of after vHIE] – [(incongruent – neutral) of before vHIE] in 1PP condition} – {[(incongruent – neutral) of after vHIE] – [(incongruent – neutral) of before vHIE] in 3PP condition}. Both values will be subjected to the McNemar test to examine the correspondence between the two incidences [66].

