## Background

It is widely known that a constant level of physical exercise is one of the key components for overall health and to postpone aging-related disorders [1–5], in somatic and cognitive terms [6–10]. Surprisingly, several recent studies have shown that aerobic exercise has beneficial consequences not only on bodily but also on cognitive functions [11–16]. Intriguingly, Kujach et al. [17] demonstrated that a high-intensity intermittent exercise (HIE)-based intervention has beneficial immediate effects on the cognitive function of sedentary young adults similar to the benefits of long-term physical adaptations [15, 18]: specifically, the HIE model they proposed consists of eight sets of 30 s of cycling exercise at 60% of the individual’s maximal aerobic power followed by 30 s of rest, for a total of 8 min. Before and after the HIE, they repeated the color-word matching Stroop task (hereinafter, Stroop task) that is widely known to measure executive functions [19–21] and they recorded with a multi-channel functional near-infrared spectroscopy (fNIRS), which allows the monitoring of cortical hemodynamic changes, specifically in the prefrontal cortex (PFC), where executive functions are localized [22, 23]. Significant behavioral improvement in inhibiting cognitive conflict induced by the Stroop-interference effect occurred after HIE and, as a neural counterpart, they found a significant increase in the cortical activation in the left dorsolateral prefrontal cortex (DLPFC) specifically after the HIE session. Therefore, this HIE-based exercise intervention may provide a strategy for improving cognitive and cardiovascular functions at the same time.

Unfortunately, in some cases, it is complicated (e.g. sedentary, very busy people, elderly in a frailty condition), sometimes even impossible (e.g. cardiopathic individuals, patients recovering after long-term disease, patients with motor impairment), to perform constant physical exercise [24] or even a short-term high-impact physical exercise. These lifestyles characterized by the absence of constant physical activity clearly have negative effects on the wellbeing of the body and, as described previously, can limit the improvement of cognitive abilities or even contribute to their decline.

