**Fig. 3 Fig3:**
[figure not shown]
The fNIRS system used in this study. **a** The headset of the fNIRS is shown on a mannequin. **b** Graphic representation of the detail and distribution of the capsules on the headset. Source: http://neu-brains.site/ [50]. Permission to reproduce the figure granted by NeU Corporation, Japan

This system is provided with 35 capsules, placed 3 cm away from each other, into which microprocessors, NIR emitting or high-sensitivity receiving sensors are packaged: the top and the bottom lines of the capsules alternate emitting and receiving sensors, while the central line comprises receivers only (Fig. 3 b); this new multi-distance measurement mode, including a total of 12 emitting and 23 receiving (11 of them are short-distance receivers) sensors, significantly reduces the biological noise on the hardware side, resulting in 34 channels over lateral and anterior PFC. The device will be positioned on the forehead by centering the specific mark on bottom line of probes at the Fpz (10% of the distance between Nasion and Inion), according to the international 10–20 system [51].

The device detects the concentration of oxygenated hemoglobin (O2Hb), deoxygenated hemoglobin (HHb), and total hemoglobin, calculated in units of millimolar-millimeter (mM·mm) [52], by applying two short-distance wavelengths of NIR light (850 nm, 730 nm) to monitor the above mentioned cortical hemodynamic changes in the PFC during the Stroop task [53].

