#### Secondary outcomes

Secondary outcomes are the data extracted from the fNIRS recording, as a neural counterpart of the behavioral measurements. We will focus specifically on O2Hb changes before and after the vHIE in the two conditions (1PP and 3PP).

In addition, we will examine the relation between Stroop task and the induced cortical activation, by means of a correlation between behavioral data from the Stroop task (RT and ER) and optical data from fNIRS. For each trial of the Stroop task (neutral, congruent, and incongruent), we will average the O2Hb data for 2 s before, 2 s during, and 10 s after the presentation of the stimulus (expecting a peak at 4–11 s after the display); also in this case, we will obtain the Stroop interference by subtracting (incongruent-neutral) O2Hb data. As for the other outcomes, the main comparison to test our hypothesis will be between 1PP and 3PP.

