#### fNIRS data

The optical data from fNIRS will be analyzed based on the modified Beer-Lambert law [57]. We will set the sampling rate at 10 Hz and analyze the difference between O2Hb and HHb signals.

We will employ the general linear model to identify O2Hb and HHb hemodynamic brain responses with reference to experimental factors. If necessary, we will combine few adjacent channels in order to create region of interest (ROI) [58] according to the LBPA40 anatomical labelling system [59].

Then, the changes in the concentration of O2Hb and HHb for each channel will be treated according to the following steps:
Excluding skin blood flow (i.e. heartbeat pulsations) from raw data by using the specific software provided.Pre-processing each channel using 0.01–0.5 Hz bound pass filter to account for the effects of Mayer waves, high-frequency fluctuations, and baseline drift [60].Performing a 3-s moving average to smooth the raw O2Hb concentrations [61, 62].We will use the color-word matching Stroop task in an event-related design which presents each neutral, congruent, and incongruent conditions in random order, so we will pick up the changes related to each condition in the concentration of O2Hb from each channel (or the combined ROIs). In particular, we will calculate the mean of the changes in the concentration of O2Hb 2 s before onset task, as a “baseline,” and 10 s after the onset of the inter-stimulus interval as “vascular response” in each Stroop task condition [46]. That will be necessary because NIRS signals are delayed with respect to participants response [46, 63].Translating the mean of O2Hb concentrations of each channel to normalized values using linear transformations, so that the mean ± standard deviation of O2Hb level in the 2 s of the baseline period is 0 ± 1 (AU). This method will be useful because of the avoidance of the influence of differential pathlength factors among the individuals and that of cortical regions [60, 64, 65].Lastly, the channels over target ROI areas, eventually, will be averaged in each Stroop task condition respectively.

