## Discussion

The background of this RCT protocol study starts with two assumptions, based on data presented in the literature: (1) HIE has acute beneficial consequences on executive functions and their neural basis [17, 67]; and (2) the movements of their own virtual body can generate measurable consequences on their real body, comparable to the ones when we actually move [33, 41].

Consequently, we hypothesized that the same HIE intervention performed by their own virtual body (and not by the real participants’ bodies) can have the same beneficial acute effects on executive functions.

In order to confirm our hypothesis, 30 healthy young adults will undergo a vHIE, where the virtual body exclusively (the real body is still sitting) will perform 8 min of training, alternating 30 s of running and 30 s of slow walking; the same vHIE will be performed in two intervention conditions: 1PP, the virtual body will be displayed with the real one, spatially replacing it, and so it will be considered as their own; in 3PP, the virtual body will be displayed 1.5 m away on the right side of the real one, and so it will simply be considered as someone else. During the vHIE, we will record the HR: we predict finding a fluctuating trend of the HR during the intervention in 1PP (and not in 3PP), coherent with the virtual movements, as if the individual is actually performing them. In addition, we will ask the participants to report verbally any subjective feelings during the intervention, predicting that increased sensations of SoBO and SoA in 1PP respect to 3PP will be found.

To test our main hypothesis about acute beneficial effects on executive functions, before and after the two vHIE intervention conditions, we will record the participants’ performance of the Stroop task; at the same time, we will record cortical hemodynamic changes over the PFC with the fNIRS. We predict finding better performance, in terms of reaction time and accuracy, in the Stroop task and higher activation of the neural correlated areas (i.e. PFC) after the vHIE in 1PP (and not after 3PP).

If we confirm our hypothesis, it means that virtual training performed only with the own virtual body can raise the same physical but especially cognitive and neural consequences of a “real” physical one.

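### If fNIRS regions are chosen on their pre-vHIE activation, the before–after (TIME) comparison is biased toward a fall, while the 1PP versus 3PP comparison is not

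*Protocol article*

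**What the plan says.** The ROI procedure appears in two places in the Protocol article.

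- **Statistical analysis, Correlations.** The first step is that "we will first investigate the cortical regions mainly activated during the Stroop task before the vHIE in both intervention conditions, as a baseline reference". Next, the (incongruent – neutral) "contrasts for the two intervention conditions will be averaged as substrates for ROI analysis". The ANOVA in all ROIs follows, "considering as factors intervention condition (1PP and 3PP) and time (before and after the vHIE"). No separate recording is named for locating the regions.
- **Statistical analysis, fNIRS data.** Here the definition is anatomical but applies only if necessary: "we will combine few adjacent channels in order to create region of interest (ROI) [58] according to the LBPA40 anatomical labelling system".

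Three other statements fix what the analysis is for. Secondary outcomes says that "the main comparison to test our hypothesis will be between 1PP and 3PP". The Discussion predicts "higher activation of the neural correlated areas (i.e. PFC) after the vHIE in 1PP (and not after 3PP"). The Background reports, from the earlier exercise study on which the design is modelled, that "they found a significant increase in the cortical activation in the left dorsolateral prefrontal cortex (DLPFC) specifically after the HIE session".

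**The concern.** A region picked because its before estimate is high will, on average, have a before estimate that is too high by chance. Its after estimate has not been selected and carries no such excess. The difference between them therefore leans toward a fall even if the vHIE does nothing. A fixed numerical threshold or a masked analyst does not remove this, because the cause is using the same data for selection and for the before level.

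Two things are at stake. TIME is a declared factor of the planned ANOVA, so its main effect will be produced and read. The Discussion also predicts an absolute rise after 1PP, which the interaction alone cannot show: a rise in 1PP with a flat 3PP gives the same interaction as a flat 1PP with a fall in 3PP. To tell these apart one must look at the changes within each condition, and those carry the bias.

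**Working it through.** **Inputs from the protocol.** 30 participants (Sample size); a montage "resulting in 34 channels over lateral and anterior PFC" (Functional near-infrared spectroscopy); selection on the before runs of both conditions, followed by a 2 × 2 repeated-measures ANOVA (Correlations). The protocol gives no figure of its own for the ROI step, so there is none to reproduce.

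**Assumed inputs, because the protocol gives none.** Run noise SD σe = 1 and stable participant-by-channel SD σs = 0.5. Between-channel noise correlation is 0 unless stated. True channel activation is none, moderate (mean 0.2, SD 0.2) or strong (mean 0.5, SD 0.3). The selection rule is the top 5 channels, the single highest channel, or all channels significant at 0.05.

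**Step 1: size of the false fall by hand.** With no true activation, the group mean of the two averaged before runs in one channel has variance (σs² + σe²/2)/n = (0.25 + 0.50)/30 = 0.025. Only the run-specific part, 0.50 of the 0.75, is not shared with the after runs. The expected after-minus-before difference is therefore −(0.50/0.75) = −2/3 of the selected before mean.
- Top 5: simulated before mean 0.237, and 2/3 × 0.237 = 0.158.
- Single highest: simulated before mean 0.322, and 2/3 × 0.322 = 0.215.

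Both match the simulated TIME bias below.

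**Step 2: why the interaction escapes.** Write B1, B3 for the before means and A1, A3 for the after means. Selection on (B1 + B3)/2 gives both before means the same expected excess δ.
- TIME = ½[(A1 − B1) + (A3 − B3)], expected bias −δ.
- Within 1PP = A1 − B1, expected bias −δ.
- CONDITION × TIME = (A1 − B1) − (A3 − B3), expected bias −δ + δ = 0.

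**Step 3: simulation with no true vHIE effect** (3,000 replicates per setting, n = 30, 34 channels).

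| True activation and rule | TIME bias (SD) | False TIME fall (nominal 2.5%) | CONDITION × TIME rejection (nominal 5%) |
|---|---|---|---|
| None, top 5 | −0.158 | 47% | 4.8% |
| None, single highest | −0.215 | 19% | 4.7% |
| None, significant channels (the 57% of replicates with any) | −0.237 | 33% | 4.8% |
| Moderate, top 5 | −0.095 | 20% | 5.9% |
| Moderate, significant channels | −0.071 | 23% | 4.9% |
| Strong, top 5 | −0.071 | 14% | 5.0% |
| Strong, significant channels | −0.023 | 9% | 5.0% |
| Moderate, top 5, channel correlation 0.5 | −0.050 | 5% | 5.7% |
| Moderate, all 34 channels, no selection | 0.000 | 2.6% | 4.4% |

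A second set of assumptions used equal true activation in all channels, the top 3 of 34, and a run-to-run correlation of 0.3.
- Independent channels: 30% false falls.
- Channel correlation 0.5: about 10%.
- Channel correlation 0.5 and run correlation 0.6: 7–9%.
- 8 regions with the top 2 taken: 4–11%.
- Selection on all four runs: 2–3% in each direction and no bias.

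**Step 4: with a true rise of 0.5 SD in 1PP only.**
- Moderate activation, channel correlation 0.5: the within-1PP estimate is 0.50 with fixed channels and 0.45 with top-5 selection. The CONDITION × TIME estimate is 0.497 either way.
- Equal activation, channel and run correlation 0.3: the within-1PP estimate falls to 0.38–0.39. Power of a within-1PP before–after test falls from 86% to 65–66%.

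**The case against.** The strongest reply is that the test the protocol relies on is sound. 1PP versus 3PP is the declared main comparison for fNIRS. The Correlations section also forms a double difference, the change in 1PP minus the change in 3PP. Selection averages the two conditions, so the false fall is equal in both and cancels. No separate before–after test within 1PP is planned, and the power loss in step 4 belongs to such a test. All of this stands.

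A reader might infer that the plan hides the predicted neural effect. The documents do not support that: a rise in 1PP beyond 3PP is estimated without bias, and only the absolute rise within 1PP is understated. A reader might also infer that selection favours a pattern of no change after 1PP and a fall after 3PP. It does not, since the expected fall is the same in both and the interaction test holds its level. Selecting on the before-1PP run alone would bias the interaction (−0.167 SD, 17% rejection in simulation with moderate activation and the top 5), but the protocol says both conditions. Because the bias runs against the hypothesis, it does not produce a false claim of benefit.

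The second reply is that selection on the before runs is an inference. The text calls this step a baseline reference, gives no threshold and does not say that other regions are dropped. The fNIRS data section points to anatomical labels. The averaged contrasts are not expressly limited to the before runs; if they cover all four, the problem does not arise. This is a fair limit on certainty. But the order of the steps, first locating the active regions and then analysing the ROIs, makes selection on the before runs the most natural reading, and the anatomical route is only conditional.

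**Conclusion.** The point holds conditionally and for a secondary outcome. If the ROIs are chosen on pre-vHIE activation, the TIME main effect and the changes within each condition are biased toward a fall. False TIME falls range from about 5% to 30% or more (47% in the most extreme setting) against 2.5% nominal. They are smaller where true activation is strong or channels are correlated. No single value in that range can be called the trial's own, because noise, channel correlation and selection rule are all assumed here. The CONDITION × TIME comparison keeps close to its 5% level throughout, and the primary Stroop RT and ER analysis does not involve ROIs. The point still deserves a change, because the absolute rise predicted after 1PP can only be read from the quantities that are biased, and the remedy is nearly free.

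**What to change.** State the ROI definition in one place and make the Correlations and fNIRS data sections agree with it. Either option removes the bias:

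1. **Fix the ROIs in advance** from the LBPA40 labels already cited, for example the channels over the left DLPFC that the Background names from the earlier exercise study.
2. **Select on balanced data:** choose the ROIs on the (incongruent – neutral) O2Hb contrast averaged over all four runs (before and after, 1PP and 3PP). This average is balanced over TIME and CONDITION, provided the variances are similar across runs.

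Under either option, say that the neural conclusion rests on CONDITION × TIME, with the changes within each condition reported to describe its direction.

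The cost is one sentence and no new data. With the second option the ROIs are known only once all runs are complete; with the first, activation outside the named region plays no part in the test.

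### McNemar's test compares two proportions, so it cannot show whether Stroop change goes with cortical or mood change in the same people

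*Protocol article*

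**What the plan says.** Secondary outcomes says that the link between the Stroop task and cortical activation will be examined "by means of a correlation between behavioral data from the Stroop task (RT and ER) and optical data from fNIRS".

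The Correlations section under Statistical analysis has two parts.

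- The first opens with "The crucial correlation for our hypothesis concerns the relationship between Stroop task and fNIRS data". It goes on to choose regions of interest (ROIs) and to run a repeated-measures ANOVA with intervention condition and time as factors.
- The second is introduced as an addition: "we will examine the relation between Stroop data and cortical activation or TDMS results in a binominal manner". The value used is a double difference, after minus before in 1PP less after minus before in 3PP, each term being incongruent minus neutral ("for each variable the following contrast will be calculated"). The test follows: "Both values will be subjected to the McNemar test to examine the correspondence between the two incidences".

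The article gives no cut-point for making the contrasts binary and does not say which test result would count as correspondence.

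**The concern.** A relation between two measures on the same people is a question about joint behaviour: do those whose Stroop interference falls more under 1PP also show the larger O2Hb or arousal change? McNemar's test addresses a different question, whether the two marginal proportions are equal. It is the only test between two measures that the article names. The companion ANOVA compares means across condition and time and gives no estimate of association between Stroop and O2Hb either.

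At stake is the claim of a neural or mood counterpart to the behavioural effect. That claim could be reported as supported or refuted on a test that does not measure it.

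**Working it through.** The article gives no figure for this analysis, so there is none to reproduce.

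**Inputs.** The number of pairs is 30 (Sample size: "We decided to recruit 30 participants to eventually control for drop-off"). Alpha is 0.05, the level the article states for the RT calculation. Assumption: each contrast is coded improved or not improved.

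**Formulas.** Let a = both improve, b = Stroop only, c = other measure only, d = neither.

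- The margins are (a+b)/n and (a+c)/n. They differ by (b−c)/n.
- Exact McNemar: p = min(1, 2 × Σ C(b+c, k) / 2^(b+c)), summed over k = 0 to min(b, c). Neither a nor d enters, and p = 1 whenever b = c, at any n.
- Association: φ = (ad − bc) / √[(a+b)(c+d)(a+c)(b+d)].

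**Tables at n = 30.**

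| Pattern | a, b, c, d | φ | McNemar p | Fisher p |
|---|---|---|---|---|
| Perfect agreement | 15, 0, 0, 15 | +1 | 1.0 | <0.001 |
| Perfect disagreement | 0, 15, 15, 0 | −1 | 1.0 | <0.001 |
| Near independence | 8, 7, 7, 8 | 0.07 | 1.0 | 1.0 |
| Exact independence, margins 80% and 50% | 12, 12, 3, 3 | 0 | 0.035 | 1.0 |

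Third row: φ = (64 − 49)/225 = 0.07. Fourth row: φ has numerator 12×3 − 12×3 = 0, and p = 2 × (1 + 15 + 105 + 455)/32,768 = 0.035.

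**Simulation.** Contrasts are assumed bivariate normal with correlation r, n = 30, tests at 0.05. The margins and correlations are illustrative; the article supplies none. Entries are rejection rates.

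| Margins | r | McNemar | Pearson on continuous contrasts |
|---|---|---|---|
| 70% / 70% | 0 | about 2–3% | about 5% |
| 70% / 70% | +0.5 | about 2% | about 83% |
| 70% / 70% | −0.5 | about 3% | about 82% |
| 50% / 50% | 0 | 2.3% | 4.6% |
| 50% / 50% | +0.5 | 2.3% | 83% |
| 50% / 50% | +0.8 | 1.5% | 100% |

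Fisher's exact test on the same binary data in the 50%/50% rows rejects in 2.4%, 33% and 88%. So a test of association responds even after dichotomising, although at r = 0.5 the cut lowers power from 83% to 33%.

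With unequal margins (contrast means 0.8 and 0 SD), McNemar rejects in 54% at r = 0 and 84% at r = +0.8. What it rejects there is equality of the margins. A strong true relation makes a finding of difference more likely.

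**Can the contrast be computed for every variable?** It needs incongruent and neutral trials. The Two-Dimensional Mood Scale section describes eight rated mood items and no trial types, so the formula cannot be applied to TDMS as written.

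**The case against.** The best defence is literal: correspondence between two incidences can mean that two proportions are equal, and McNemar does test that. The article also cites earlier studies for the approach, and a fuller plan could name the correlation coefficient that Secondary outcomes promises. None of this rescues the choice. The same paragraph states its aim as the relation between the measures, and precedent does not change what a test measures.

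Several stronger readings are tempting but unsupported.

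- A reader might infer that the authors would take a non-significant McNemar result as proof of correspondence. The article does not say so. The tables show that neither direction would work.
- A reader might infer that McNemar is itself the crucial correlation. That phrase opens the paragraph leading to the ANOVA; McNemar is presented as an addition to it.
- A reader might infer that the main efficacy conclusion is compromised. It is not. The primary outcome is Stroop RT, then ER, analysed by a time-by-condition ANOVA, and the sample size rests on RT.
- A reader might take 83% as the power the trial would gain. It assumes r = 0.5 between observed contrasts. Each contrast is a repeated difference built on 10 trials per trial type per run, and measurement noise would weaken the observed correlation.

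**Conclusion.** The point holds as a should-fix. McNemar's test does not answer the question set for it. With equal margins its result hardly depends on the association, and with unequal margins it can be significant when there is none. The exact tables need only 30 pairs and a binary coding; the simulated rates also rest on the assumed normality, margins and correlations. The consequence is confined to the secondary analysis relating Stroop change to O2Hb and to TDMS.

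**What to change.** Replace McNemar's test with a Pearson or Spearman correlation, with 95% CI, of the undichotomised per-person contrasts: Stroop RT (and ER) against O2Hb in the ROIs. The article refers to all ROIs, so either name the target ROI beforehand or correct for multiplicity. State the sign convention, since the predicted benefit is a fall in RT interference and a rise in activation.

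For TDMS, use the after-minus-before change in 1PP minus that in 3PP, building on the change score already described under TDMS data.

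If binary values are kept, state the cut-point and use φ with Fisher's exact test, or kappa.

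Interpret the interval, not only the p-value. With 30 people and an observed r of 0.5, Fisher's z gives 0.549 ± 1.96/√27 = 0.172 to 0.926, or r from 0.17 to 0.73.

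The cost is analysis wording and one added TDMS contrast. No new data are needed.
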